**Primary Outcome**

**Feasibility.** will be measured through recruitment rate, retention rate, and adherence (41).

**1. Recruitment rate.** Recruitment rate will be calculated as the percentage of participants who enroll in the study out of the total number of eligible participants (23). Reasons for nonenrolment and ineligibility for the study will also be recorded. A recruitment rate of >50% is considered moderate (40).

**2. Retention rate.**  Retention rate will be calculated as the percentage of participants who complete the study (i.e., receive the full dose of the intervention and provided post-test outcome data) out of the number of participants who were enrolled (i.e., signed a consent form and provided baseline data) (41). A retention rate of ≥80% is considered high (40).

**3. Adherence.** Participants’ adherence will be determined by: 1) the number of treatment sessions attended; and 2) the level of engagement with the treatment (41). For this study, the planned number of sessions is five per week for 6 weeks for a total of 30 sessions. Thus, client adherence will be measured in two ways: 1) as a percentage: the number of sessions attended divided by the total number of sessions (30 sessions); and 2) a) the duration of each walking session, duration of each intervention session, and number of sit to stands done per session; and 2) b) the number of sit to stands done per session, divided by the goal number of sit to stands (see Table 1). Participant’s adherence to treatment will be documented by the interventionist using an adherence checklist created for this study (Appendix S) immediately after each intervention session. An adherence of ≥75% is considered high (28).

**Intervention fidelity.** Intervention fidelity will also be measured through the interventionist’s self-report of 12 intervention items (41). The percentage will be calculated as the number of items done divided by the 12 items on the intervention fidelity checklist. Immediately after each session, the interventionist will document the specific activities provided during the session using a structured checklist (Appendix S) created for this study, which includes the specific activities that were done during each session. Any safety events (such as falls) that occur during the intervention sessions will also be documented.

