**Protocol Summary**

**The OASIS Walking Study - Older Adults with cognitive impairment performing SIt to Stands and Walking in a transitional care unit: a feasibility Study**

**Sample size**: n = 26 patient participants and their SDM (Total 52).

**Study population**: older adults ≥65 years admitted to one of two facility-based TCUs

**Study design**: A feasibility study using a quasi-experimental one-group repeated measures design will be conducted.

**Study duration**: December 2023-July 2024

**Study objectives**: The proposed study has two objectives:

1) To determine the feasibility of and satisfaction with the OASIS Walking Intervention in older adults with CI in two facility-based TCUs.

2) To determine the efficacy of the OASIS Walking Intervention on older adults’ muscle strength, mobility, functional status, quality of life, and discharge destination.

**Endpoints of the study**: The study is expected have direct value to older adult patients and their care partners. If shown to be efficacious, the study can also decrease care requirements for patients within the TCP and when they return home or when they are discharged to long-term care, which ultimately would be expected to help the health care system. The ultimate goal is to promote continued functioning, mobility, and improved quality of life for older Canadians.

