**Study Hypotheses**

- It is hypothesized that the OASIS Walking Intervention will be feasible as evidenced by a moderate recruitment rate (>50%), high retention rate (≥80%), and high adherence rate (attendance to ≥75% of all intervention sessions) (28).
- It is hypothesized that the participant satisfaction will be high (Client Satisfaction Questionnaire (CSQ) of 3 or more on all CSQ items) (33).
- It is hypothesized that the OASIS Walking Intervention will result in improved muscle strength (reduction in the time to perform one sit to stand by ≥0.87 seconds, p=0.01 (31), mobility (minimum detectable change (MDC) ≥9.1 meters on two-minute walk test (34)), functional ability (≥1 point improvement in Barthel Index (BI) considered as clinically meaningful (35)) in older adults with CI in facility-based TCPs, and quality of life (minimally clinical important difference is an increase in 3 points (36)).

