## Setting

Transitional Care Unit (TCU) in Abbeylawn Retirement home in Pickering, Ontario and TCU in Cedarbrook Lodge Retirement Home in Scarborough Ontario. The Abbeylawn TCU admits patients designated as ALC and are destined to go to long-term care and has a 35-bed capacity. From December 2023-May 2024 (or, for 6 months from the actual start date of the study), patients will be enrolled in the study on an ongoing basis. Up to 8 patients will be enrolled in the study at a given time.

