# OUTCOME MEASURES

**Data Collection**

Demographic variables, including age, sex, gender, race/ethnicity, education, socioeconomic status, highest level of education, and number of co-morbidities will be collected before the start of the intervention (Appendix E). Data on hospital admission diagnosis and length of hospital stay prior to TCP admission will also be collected (Appendix E). Demographic data and outcome data at T1 will be obtained within the first month of the patient’s admission to the TCU.

Table 2 outlines the outcome measurement tools that will be used to assess the participants, time points at which they will be measured, and the type of statistical test that will be used to analyze the results. The total expected time for tests is 37 minutes at T1, and 29 minutes at T2 and 45 minutes at T3.

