# STATISTICS

**Sample Size**

An activity-based study involving older adults with dementia in the nursing home setting (31) that used time to perform one sit to stand found a moderate effect size (Cohen’s d) of 0.48. Since the present study will use repeated measures ANOVA, a Cohen’s *f* of 0.25 (a suggested value for moderate effect size) (55) was used in the sample size calculation. Based on an *f* of 0.25, a power of 0.8 and an alpha of 0.1, in keeping with those used in a mobility study involving older adults with dementia (23), a sample of 21 participants will be needed for this study. Using an alpha of 0.1 can be acceptable for exploratory or preliminary studies (56) (p. 188). An attrition rate of just under 20% over the course of a 6-week study will be taken into account, as was experienced in a 6-week intervention study involving older adult residents with dementia (28). Thus, a sample of 26 participants will be recruited for this study. G*Power 3.1.9.7 software (57) was used for the sample size calculation for an ANOVA: Repeated measures, within factors statistical test with one group, three measurements, 0.6 for the correlation among repeated measures, and 0.8 for nonsphericity correction (which is a mild departure from sphericity) (56).

The sample size is achievable based on input provided by our collaborating TCP administrators, as the TCP has a 35-bed capacity and most patients have cognitive impairment.

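### The recruitment rate counts every eligible patient, but places are limited to 8 at a time and 26 in total, so lack of places can lower the rate tested against >50% in the same way as refusal

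*Protocol*

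**What the plan says.** Protocol, Primary Outcome, fixes the formula: "Recruitment rate will be calculated as the percentage of participants who enroll in the study out of the total number of eligible participants". It adds: "Reasons for nonenrolment and ineligibility for the study will also be recorded". Protocol, Study Hypotheses, sets the target: "a moderate recruitment rate (>50%), high retention rate".

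The limits on the numerator stand elsewhere. Protocol, Setting: "Up to 8 patients will be enrolled in the study at a given time". Protocol, Sample Size: "Thus, a sample of 26 participants will be recruited for this study". The Protocol Summary repeats the 26: "n = 26 patient participants and their SDM (Total 52"). The 52 in that line is patients plus decision-makers and has nothing to do with the 52 eligible patients discussed below.

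Three timing statements also matter. The intervention lasts six weeks (Intervention Dose). Recruitment runs for six months at two units (Recruitment Sites). The Data Collection section limits how long a patient can wait for baseline: "outcome data at T1 will be obtained within the first month of" the admission to the unit. The retention paragraph of Primary Outcome treats a patient as enrolled only after consent and baseline data.

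**The concern.** The numerator is bounded by delivery capacity and by a fixed sample. The denominator, as written, has no bound. A patient who meets the criteria while all 8 places are taken, or after the 26th enrolment, may add one to the denominator with no chance of adding one to the numerator. The reasons for non-enrolment are recorded, but the formula does not use them.

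Recruitment is one of three primary feasibility measures, and the Protocol (Gap in the Literature) says that feasibility studies inform the decision to move to the next stage. A low rate caused by refusal and a low rate caused by full places call for different responses. The stated ratio cannot tell them apart, and a busier site would look worse.

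**Working it through.** **The plan's own figures.** For a repeated-measures ANOVA within factors, with f = 0.25, alpha = 0.10, 3 measurements, correlation 0.6 and nonsphericity 0.8, the noncentrality is f² × n × 3 × 0.8/(1 − 0.6). At n = 21 this is 0.0625 × 21 × 3 × 0.8/0.4 = 7.875. Power is 0.792 at n = 20 and 0.811 at n = 21, so 21 is reproduced. With attrition just under 20%, taken as 19%, 21/0.81 = 25.9, which gives 26. The ceiling on the numerator is therefore 26, as stated.

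**Effect of the total of 26.** Rate = 26/E, where E is the number counted as eligible and everyone offered a place accepts:

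- E = 30: 86.7%
- E = 40: 65.0%
- E = 51: 51.0%
- E = 52: 50.0%, which misses a strict >50%
- E = 60: 43.3%
- E = 80: 32.5%

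Fifty-two in 26 weeks is 2 per week.

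**Effect of the 8-place limit alone.** Eight places held six weeks each serve 8/6 = 1.33 patients per week in steady state. The rate falls to 50% at twice that, 16 eligible patients per six weeks or about 2.7 per week. Over 26 weeks the places can serve 8 × 26/6 ≈ 34.7, so the limit does not prevent reaching 26.

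**Can patients wait?** If all 8 started on the same day, no place would open by completion for 42 days. With a month taken as 30 days, patients admitted in the first 42 − 30 = 12 days would miss the baseline window. The Setting section says enrolment is ongoing, however. With evenly staggered starts, a place opens about every 42/8 = 5.25 days, and waiting usually works.

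**Simulation.** Assumptions: random (Poisson) arrivals of eligible patients over 26 weeks, 8 places held 42 days, at most 26 enrolled, 100% acceptance, no early withdrawal. The arrival rates are assumed, since the Protocol gives none. Entries are the share of runs with a rate of 50% or less.

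| Eligible per week | Expected in 26 weeks | Counting all 26 weeks, no waiting | Counting stops at 26th enrolment, no waiting | Counting stops at 26th enrolment, waiting up to 30 days |
|---|---|---|---|---|
| 1 | 26 | 0% | 0% | 0% |
| 1.5 | 39 | 2–3% | under 1% | 0% |
| 2 | 52 | about 52% | 6% | 1–2% |
| 2.5 | 65 | 96% | 47% | 25% |
| 3 | 78 | 100% | 88–89% | 72–74% |

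If counting runs the full 26 weeks, waiting makes almost no difference (still about 52% at 2 per week), because the total of 26 is then what binds.

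**The case against.** The best defence is that the unbounded denominator is an inference. Under Inclusion criteria, eligibility needs two clinical clearances and a willing care partner, and under Recruitment and Consent Process the interventionist confirms the criteria after first contact. A patient not worked up because places are full might never be counted. That reading is possible, but the same section speaks of eligible patients being told of the study by unit staff, before confirmation. The text supports both denominators, and they can give opposite answers against >50%.

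It can also be said that screening normally ends when the sample is complete. If so, the effect of the 26 disappears. The Protocol does not say it, and the 8-place effect remains at higher arrival rates. Leaving the counting rules to an analysis plan is common, but here the Protocol itself states the formula.

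Two further points stand and limit the priority. Recruitment is analysed descriptively with no stop/go rule attached. Recorded reasons for non-enrolment would also let a careful analyst recalculate the rate afterwards.

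A reader might infer that the criterion is likely to fail. The documents do not support that. Take 35 beds, an assumed 60-day stay and half the patients with cognitive impairment. Then 35 + 35 × 182/60 ≈ 141 patients pass through the larger-documented unit, about 71 with cognitive impairment; with no turnover the figure is about 18. Neither number counts eligible patients. Reaching 52 from 71 needs 52/71 = 73% to pass every other criterion; if one third pass, about 24 are eligible. The stay is assumed, some initial residents would already be past the baseline window, and the size of the second unit is not given.

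**Conclusion.** The point holds as a defect of definition. A stated primary feasibility formula mixes lack of places with refusal, and nothing in the Protocol separates them or closes the count. The exact part is that 26 enrolled out of 52 or more counted as eligible cannot exceed 50%.

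How likely this is depends on an eligible-patient rate that the Protocol does not give and on two unstated counting rules. On the favourable reading (staggered entry, waiting within the one-month baseline window, counting stopped at the 26th enrolment), failure for this reason is near zero up to 2 eligible patients per week and becomes material at about 2.5 to 3. On the unfavourable reading it is about even at 2 per week. It would be wrong to conclude that the criterion will fail, or that the 8-place limit by itself shuts patients out of the baseline window, since that needs all 8 to start together. Priority is low to moderate.

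**What to change.** In Primary Outcome, state that the rate compared with >50% is participants enrolled divided by eligible patients identified while a place was open, or who could be given one in time for baseline within the first month of admission. State that counting ends at the 26th enrolment. Report beside it the number of eligible patients not enrolled for lack of a place, and the rate over all eligible patients as now defined.

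The cost is one or two sentences and a no-place-available code among the reasons for non-enrolment, which are already recorded. Sample size, eligibility and intervention are unchanged. The downside is that the main rate no longer describes the whole eligible population, which is why the overall rate and the separate count stay in the report.

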## Inclusion criteria

Older adults will be eligible if they meet the following criteria: 1) aged 65 years and older;

2) have cognitive impairment (dementia, delirium, cognitive impairment, or unspecified cognitive impairment) as documented in the medical record or Quick Dementia Rating Scale (QDRS) score of ≥2) (Appendix A); 3) admitted to a transitional care unit after a hospitalization; 4) can speak English; 5) has received clearance from the physiotherapist to participate in the study; 6) has received clearance from the nurse practitioner to participate in the study; 7) were community-dwelling (lived in a home or retirement home; not a nursing home) prior to hospitalization; 8) Were able to walk independently or with the assistance of one person (with or without a gait aid) prior to hospital admission; 9) is currently able to ambulate either independently or with the assistance of one person (with or without a gait aid); 10) has a care partner (family member, friend) who is willing participate in an interview about the patient for the study.

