**Recruitment and Consent Process**

Patients: Eligible patients will be informed of the study by the TCP manager, admitting clerk, or designated staff member and ask if they are willing to have the research personnel to contact them to tell them more about the study. The interventionist (AC) will confirm eligibility, obtain consent and enroll patients into the study.

In order to confirm eligibility for the study, the interventionist will check with the unit physiotherapist (PT) and nurse practitioner (NP) to see if the patient is cleared for the study. After receiving clearance from the PT (Cedarbrook PT Clearance Form and Abbeylawn PT Clearance Form) and NP (NP Clearance Form), the interventionist will confirm with the patient and chart that they have met all eligibility criteria for the study (Appendix O – Check for Eligibility by Interventionist).

To assess the patients’ ability to provide consent, the interventionist will use a validated evaluation to sign consent (ESC) measure (Appendix M) (61). After going over and explaining the consent form, the interventionist will ask the patient to 1) identify potential risks, 2) summarize what is expected of them, the patient, 3) what they would do if they no longer want to participate in the study, 4) what if distress or discomfort associated with participating in the study is experienced. If the patient can correctly answer these questions and understand the consent form (answer in their own words), they will be asked to sign the consent form. Before asking the questions, the interventionist will make a subjective judgement whether the patient is alert and able to communicate, however if the patient no longer appears alert and able to communicate when the questions are asked, the interventionist will return to the first question, put a line through ‘yes’ answer, enter initials and date, and check no. The patient will not be considered capable to consent to participation in the study (61). For those individuals who pass the ESC, informed written consent will be obtained.

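### The recruitment rate is biased upward because a care partner's refusal makes the patient ineligible and removes them from the denominator

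*Protocol*

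**What the plan says.** In the Protocol's Primary Outcome section, feasibility "will be measured through recruitment rate, retention rate, and adherence". The first of these is defined as follows: "Recruitment rate will be calculated as the percentage of participants who enroll in the study out of the total number of eligible participants". The same section adds: "A recruitment rate of >50% is considered moderate". Study Hypotheses uses that figure as a target: the intervention will be "feasible as evidenced by a moderate recruitment rate (>50%), high retention rate (≥80%), and high adherence rate".

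Eligibility is set by ten inclusion criteria. Item 10 is that the patient "has a care partner (family member, friend) who is willing participate in an interview about the patient for the study".

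The Recruitment and Consent Process gives the sequence:
- Unit staff tell patients about the study and "ask if they are willing to have the research personnel to contact them to tell them more about the study". The sentence already calls these patients eligible.
- The interventionist then "will confirm eligibility, obtain consent and enroll patients into the study".
- Once the physiotherapist and nurse practitioner have given clearance, "the interventionist will confirm with the patient and chart that they have met all eligibility criteria for the study".
- For a patient who cannot consent, the substitute decision-maker (SDM) is asked to get in touch, consents to enrolment, and names a care partner. If that is another person, the SDM approaches them, and they give their own consent.

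The Ethics section places the consent-capacity assessment after the eligibility criteria have been met. The Primary Outcome section also has the team log why patients were ineligible or not enrolled.

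**The concern.** A recruitment rate should show how many suitable patients the study can actually bring in. Item 10 is not a patient characteristic like age or walking ability. It is another person's agreement to a study procedure. The Protocol itself treats it so: the care partner signs a consent form, the interview feeds the communication care plan that is Component 1 of the intervention, and the Remuneration section provides a gift card for it. A care partner who declines has refused part of the study.

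Because that agreement sits inside eligibility, the refusal is filed as ineligibility and the patient leaves the denominator. The recruitment rate is one of three primary feasibility measures, and it is compared with a numeric target. The Protocol's Gap in the Literature section says that a feasibility study informs progression to the next stage. A later trial with the same care-partner requirement would meet the same refusals, and the stated rate would not show them.

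**Working it through.** **Where each kind of loss falls, on the text**

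| Loss | In the denominator? | Basis |
|---|---|---|
| Care partner unwilling | No | Fails item 10, so not eligible |
| Care partner (not the SDM) declines after SDM consent | Not stated | Item 10 fails late; no counting rule is given |
| Patient declines research contact | Ambiguous | Called eligible at first approach, but eligibility is confirmed later, with the patient |
| SDM does not respond | Not stated | No counting rule is given |
| Consent refused after eligibility is confirmed | Yes | Consent follows eligibility |

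**Inputs from the Protocol**
- Rate = enrolled / eligible; target >50% (Primary Outcome, Study Hypotheses).
- Planned enrolment 26 (Sample Size).
- No count of eligible patients or refusals is given. Both are assumed below.

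**The planned 26 reproduces.** The Sample Size section uses f = 0.25, alpha 0.1, power 0.8, m = 3 measurements, correlation 0.6 and nonsphericity 0.8. The noncentrality is f² × N × m × 0.8 / (1 − 0.6). For N = 21 this is 0.0625 × 21 × 3 × 0.8 / 0.4 = 7.875, with 1.6 and 32 degrees of freedom. Power is 0.811 at N = 21 and 0.792 at N = 20, so 21 is right. With 19% attrition, 21 / 0.81 = 25.9, so 26. The recruitment point does not depend on this calculation; it only borrows the 26.

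**Direction.** Let D be the patients counted as eligible, and R the otherwise eligible patients removed because a care partner refused. The stated rate is 26/D. The rate that counts those refusals is 26/(D + R). For any R > 0 the first is larger, so the bias is always upward.

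**Size, over assumed D and R.** With 26 enrolled, the rate exceeds 50% only if the denominator is below 52, that is, 51 or fewer.

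| D (assumed) | Stated 26/D | R = 5 | R = 10 | R = 15 | R = 20 | R at which >50% is lost |
|---|---|---|---|---|---|---|
| 35 | 74.3% | 65.0% | 57.8% | 52.0% | 47.3% | 17 |
| 40 | 65.0% | 57.8% | 52.0% | 47.3% | 43.3% | 12 |
| 45 | 57.8% | 52.0% | 47.3% | 43.3% | 40.0% | 7 |

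The last column is 52 − D. At D = 40, 12 uncounted refusals give 26/52 = 50.0%, which is not above 50%.

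**The same in shares.** Let s = R/(D + R). Then the rate counting refusals = stated rate × (1 − s), and it reaches 50% at s = 1 − 0.50/(stated rate):
- stated 60%: s = 1 − 0.50/0.60 = 16.7%
- stated 65%: s = 1 − 0.50/0.65 = 23.1% (12 of 52)
- stated 70%: s = 1 − 0.50/0.70 = 28.6%

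**The case against.** Enrolled over eligible is a standard definition. The care-partner interview also shapes the intervention, so a patient without one cannot receive it as designed, and uptake among patients who can receive it is a legitimate quantity. The reasons for ineligibility are to be logged, so an alternative rate could be derived. The >50% is a hypothesis and a label; no section ties a progression decision to it.

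Much of this stands. It limits how strongly the point can be put, and the log makes the repair cheap. But the log does not put these patients into the rate. A rate restricted to patients with a willing care partner answers a narrower question than whether the study can recruit on these units, and the Protocol does not say that it is so restricted.

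A reader might go further and infer that refusals in general leave the denominator, including those of patients who decline research contact. The documents do not support that. The sentence describing the first approach already calls the patients eligible, so on that wording someone who declines contact is eligible and not enrolled. Only the later confirmation step points the other way. Refusals of consent after confirmation are counted. In the SDM route, a care partner may be approached after the SDM has consented, and nothing says that the patient is then reclassified as ineligible.

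**Conclusion.** The point holds for care-partner refusals. Under item 10 and the definition of the rate, they are classed as ineligibility and raise a primary outcome. This does not depend on which stage is meant by eligible, except in the SDM route, where the treatment of a late refusal is unstated. For patients who decline contact, the denominator is undefined rather than wrong.

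The direction is certain and the size is not. Every figure beyond the 26 and the >50% is assumed, and it is also assumed that exactly 26 enrol. Within the range shown, 7 to 17 uncounted refusals would take the rate from above the target to 50%. A reader might conclude that the target will be met only because of the definition; with no refusal counts in the documents, that cannot be said.

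The Protocol itself fixes the formula, the eligibility list and the target, so this is not a detail left to an analysis plan.

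**What to change.** - Keep item 10 as a condition of enrolment, but take it out of the definition of eligible used for the recruitment rate.
- Count as eligible but not enrolled: care-partner refusal (including refusal after SDM consent), SDM non-response, and refusal of consent.
- State that eligible is fixed at first approach, on the criteria that unit staff can judge from the chart.
- Have unit staff keep an anonymous count of patients who decline contact. Show it in the participant flow, and give a sensitivity rate that includes them. They need separate handling because physiotherapist and nurse practitioner clearance (items 5 and 6) will generally be unknown for them. Adding all of them to the main denominator would include some patients who might not have been cleared, and would push the rate down.

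The cost is a change of wording and a small tally by staff who already make the first approach; reasons for non-enrolment and ineligibility are already to be recorded. The stated rate may look less favourable. The change is best made before enrolment starts, since refusals that nobody logged may not be recoverable.
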